### Statistical analysis

In this trial, our primary outcome measure is the Tinnitus Handicap Inventory. We define the treatment response as a reduction in score on the Tinnitus Handicap Inventory following treatments of 20 points or more. First, baseline characteristics will be analyzed using descriptive statistics for each group. Then repeated measures analysis is performed to make comparisons among the treatment groups and the control group (ABVN plus tone versus electrical acupuncture, non-ABVN plus tone versus electrical acupuncture, and ABVN versus electrical acupuncture) at different time points (4th, 8th, and 12th week). If a significant difference is found, the next step is to make comparisons among the three treatment groups in effectiveness. Multiple comparisons will be adjusted according to the Bonferroni correction method. The Kruskal-Wallis test will be employed in the analysis of skewed distribution data. Analysis of variance will be used for numerical variables, and the *χ*^2^ test for categorical variables.

Statistical analysis will be performed by the Medical College of China Three Gorges University, [name]. The statistician is blinded from the allocation of groups. The SPSS 15.0 software package (SPSS Inc., Chicago, IL, USA) will be used to analyze the data.

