### Primary outcome measures

The primary outcome is evaluated using the Tinnitus Handicap Inventory, which evaluates 25 items grouped into a functional subscale (11 factors), an emotional subscale (9 factors), and a catastrophic subscale (5 factors). Each question of the Tinnitus Handicap Inventory can be answered by either ‘often’ (4 points), ‘sometimes’ (2 points), or ‘never’ (0 points). The total score allows the tinnitus to be categorized as: ‘slight’ (0 to 16 points), ‘mild’ (18 to 36 points), ‘moderate’ (38 to 56 points), ‘severe’ (58 to 76 points), or ‘catastrophic’ (78 to 100 points). The assessment is at baseline (before randomization), and in the 4th and 8th week, with further follow-up visits after termination of the treatment at the 12th week.

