### Statistical methods

The trial aims to detect a difference between the four study groups. We present here our power analysis for the primary outcome only. This is deemed a clinically significant difference of a 20-point or greater reduction in score on the Tinnitus Handicap Inventory following treatments. Since this is a novel therapy, we used data from a previous proof-of-concept feasibility study [21], the mean decrease rate is 28% in the VNS group and 0.97% in the control group.

The following formula was used for a four-group trial [22]:$$ {n}_1={n}_2=\frac{{\left({\mu}_{\alpha }+{\mu}_{\beta}\right)}^22P\left(1-P\right)}{{\left({P}_1-{P}_2\right)}^2} $$

Calculations are performed using 80% power and a 5% significance level (two-side). The required sample size is approximately 27 participants for each group. Assuming a 10% dropout rate, we plan to enroll a total of 120 participants with four groups of equal size (30 participants per group).

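### The trial is sized on a 20-point THI response, but the only group comparison spelled out is a repeated measures analysis, and nothing rules out claiming success on the response instead

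*Protocol article*

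**What the plan says.** **Primary outcome measures** names the instrument and describes its scoring and severity bands: "The primary outcome is evaluated using the Tinnitus Handicap Inventory, which evaluates 25 items". It gives no responder threshold.

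**Statistical methods** says "We present here our power analysis for the primary outcome only" and goes straight on: "This is deemed a clinically significant difference of a 20-point or greater reduction in score on the Tinnitus Handicap Inventory following treatments". It then applies a formula for comparing two proportions, with 28% and 0.97% as inputs, a two-sided 5% level and 80% power. The result is about 27 per group, raised to 30 per group (120 in total) for 10% dropout.

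**Statistical analysis** opens with "In this trial, our primary outcome measure is the Tinnitus Handicap Inventory" and follows at once with "We define the treatment response as a reduction in score on the Tinnitus Handicap Inventory following treatments of 20 points or more". The comparison comes next: "Then repeated measures analysis is performed to make comparisons among the treatment groups and the control group". Three contrasts against electrical acupuncture and three visits (weeks 4, 8 and 12) are listed, and Bonferroni is named for multiple comparisons. The section ends with tests by type of variable: Kruskal-Wallis for skewed data, "Analysis of variance will be used for numerical variables", and chi-square for categorical variables.

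**The concern.** A primary outcome should have one form that is sized, tested and used to judge the trial. Here a binary response appears in the sample size and again beside the primary outcome in the analysis section, while the comparison described is of a repeatedly measured quantity. Two things follow.

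- The 80% power was worked out for a comparison of proportions. It says nothing about the power of the repeated measures comparison, which needs an SD and a mean difference that the article does not state.
- If the score comparison misses significance and the responder comparison does not, nothing in the text prevents the second being reported as the primary result. Bonferroni is introduced for comparisons between groups and does not reach a choice between two forms of one endpoint.

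This is separate from which visit is decisive and from whether the formula was given suitable inputs. It would remain with one visit and correct inputs.

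**Working it through.** **1. The article's own figure.** Inputs from Statistical methods: P1 = 0.28, P2 = 0.0097, two-sided 5%, 80% power.

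- P = (0.28 + 0.0097)/2 = 0.14485
- n = (1.960 + 0.842)² × 2 × 0.14485 × 0.85515 / (0.28 − 0.0097)² = 26.6, so 27 per group
- 27/0.9 = 30 per group, and 4 × 30 = 120

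The stated size reproduces, as a comparison of two proportions at an unadjusted 5%.

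**2. Where each form appears.**

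| Section | Form of the THI outcome |
|---|---|
| Primary outcome measures | Scored inventory, no threshold |
| Statistical methods | Fall of 20 points or more; two-proportion formula |
| Statistical analysis, response definition | Fall of 20 points or more |
| Statistical analysis, group comparison | Repeated measures; dependent variable not named |
| Statistical analysis, tests by type | Chi-square for categorical variables; no endpoint named |

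No sentence ranks the two forms or labels either supportive.

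**3. The 80% does not carry over to the score.** The article gives no THI SD, so the values here are assumed. Simulation: 20,000 two-arm comparisons per setting, 27 per arm, normal reductions, control mean reduction 5, t test on the reduction, two-sided 5%. Power for the score ran from 14.7% (SD 20, difference 5) to 99.9% (SD 10, difference 15). At SD 15 and difference 10 it was 67.0%. The figure depends wholly on inputs that the article does not fix.

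**4. False positives if either form may be claimed.** Assumptions: normal reductions, no true difference, control mean 5 to 15, SD 15 to 20, 27 to 30 per arm, one visit. Tests: t test on the reduction and chi-square on a reduction of 20 points or more. Two independent 5% tests would give 1 − 0.95² = 9.75%. These two are correlated (about 0.65 to 0.79), so the rate is lower.

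| Setting | Score alone | Either form | Either form, continuity-corrected chi-square |
|---|---|---|---|
| One contrast at 5% | 5% (nominal) | about 7% to 9% | about 6% |
| Three contrasts, each at 0.05/3 = 0.0167 | 4.1% to 4.6% | 6.5% to 7.6% | 5.0% to 5.6% |

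**5. How often the forms disagree.** With a true advantage of 10 to 15 points, 27 per arm, the Bonferroni level and the same ranges, one form is significant and the other is not in about 17% to 33% of trials. Responder-only significance makes up 1% to 4% of trials. The rest is score-only, because the score has more power: about 61% to 63% against 43% for a 15-point advantage with SD 20 and control mean 10.

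The direction depends on the shape of the effect. If only a quarter of the active arm benefits strongly (mean 30, SD 10) and the rest behave like controls (mean 5, SD 10), then at two-sided 5% the responder form is significant more often (50.5% against 41.9%). Disagreement is then 26.1%, of which 17.4 points are responder-only.

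**The case against.** The best reply is that the plan has one confirmatory path. Repeated measures is the only THI comparison spelled out, with its contrasts, its visits, a gate to the next step and a Bonferroni adjustment. The outcome section describes a score. The chi-square sentence is a generic list by variable type, names no responder comparison, and could serve baseline categories. The 28% and 0.97% are described as mean rates of decrease, not shares of responders, so even the sample size is not cleanly a responder calculation. Ranking analyses is often left to a SAP.

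Much of this stands. A reader might infer that the plan sets up two formal tests of the primary outcome with equal claims to decide. The documents do not support that, because no responder comparison is assigned. A reader might also infer that response is properly powered as the primary endpoint, and the wording of the inputs does not support that either.

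What the reply does not remove is the mismatch in the printed text. The power section says that it concerns the primary outcome and attaches the 20-point fall to it. The analysis section repeats the definition directly under the primary outcome. The repeated measures sentence does not name its dependent variable. This is more than detail deferred to a SAP, since the article itself attaches both forms to the primary outcome.

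The size is also open to challenge. Every SD, mean and distribution is assumed, and a single-visit t test stands in for the multi-visit analysis. A continuity-corrected chi-square removes most of the excess error.

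**Conclusion.** The concern holds as a mismatch between the form of the primary outcome that was sized and the form whose analysis is described, with an unclosed route to claiming success on the other form. That the stated 80% power does not apply to the described analysis follows from the text and needs no assumption.

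The error-rate consequence is real but modest. Under the assumed ranges the family-wise rate is at most 7.6 − 5.0 = 2.6 percentage points above 5%, and at most 0.6 points above it with a continuity-corrected chi-square.

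It would be tempting to say that the two forms can give opposite verdicts. The calculation shows only that one may be significant while the other is not. With a uniform shift this is mostly the score's greater power, and switching to response would rescue a missed score result in only 1% to 4% of trials. An effect confined to a minority of patients could make it more frequent.

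**What to change.** - In Primary outcome measures and Statistical analysis, state that the THI total score from the repeated measures comparison is the single primary endpoint and alone decides the trial.
- Label the 20-point response a supportive secondary analysis, reported as proportions and differences with confidence intervals.
- In Statistical methods, restate the power for the planned 27 to 30 per arm on that score, giving the assumed SD and difference.

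This changes wording and one power statement. It needs no new data or patients. The price is that a significant responder result alone could no longer be claimed as a positive trial.

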### Types of participant

#### Inclusion criteria

Qualified participants meeting all of the following conditions will be recruited [18,19]:Single-tone subjective tinnitus, typical conditions of unilateral or bilateral;Age 15 to 65 years, either sex;Recurrent attacks for more than 1 month or persist attacks for more than 5 days;Must be able to hear stimulation tones presented by the device at all frequencies;Must be able to complete the forms and use the rating scales;Not be taking part in any other clinical trial during the period;Voluntarily signed informed consent forms.

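### Response requires a 20-point THI fall, but entry sets no minimum THI, so a participant starting at 18 or less is a non-responder by construction

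*Protocol article*

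**What the plan says.** Three parts of the protocol article bear on this point.

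- **Response.** Statistical analysis says: "We define the treatment response as a reduction in score on the Tinnitus Handicap Inventory following treatments of 20 points or more". Statistical methods uses the same threshold for the power analysis: "This is deemed a clinically significant difference of a 20-point or greater reduction in score on the Tinnitus Handicap Inventory following treatments".
- **Scale.** Primary outcome measures describes 25 items, each scored "often’ (4 points), ‘sometimes’ (2 points), or ‘never’ (0 points". The two lowest severity bands are "slight’ (0 to 16 points), ‘mild’ (18 to 36 points". THI is assessed at baseline, before randomization.
- **Entry.** The inclusion list opens with "Qualified participants meeting all of the following conditions will be recruited". Its disease criteria are "Single-tone subjective tinnitus, typical conditions of unilateral or bilateral" and "Recurrent attacks for more than 1 month or persist attacks for more than 5 days". The other conditions cover age, hearing the stimulation tones, ability to complete the forms and scales, not being in another trial, and consent. The exclusion list covers other causes of tinnitus, comorbidity, inability to use the forms, and pregnancy. Neither list contains a THI score or any other severity threshold.

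**The concern.** The rule for who may enter and the rule for what counts as success do not fit together. The largest possible fall in THI is the baseline score itself, so some eligible people cannot meet the response definition. They occupy places in groups of 30, lower the highest response rate any arm can reach, and shrink the difference in response proportions between arms. The sample size has almost no slack on its own formula, so even a small share of such participants takes power below the stated 80%.

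**Working it through.** **1. Who cannot respond.** With 25 items scored 0, 2 or 4, the total is an even number from 0 to 100. The largest fall equals the baseline. A fall of 20 is therefore impossible from 0, 2, 4, 6, 8, 10, 12, 14, 16 or 18, which is the whole slight band plus the lowest mild score. The lowest baseline from which response is possible is 20, and that participant must reach 0. A participant at 36, the top of the mild band, must lose 20/36 = 56% of the score.

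**2. The plan's sample size.** Inputs from Statistical methods: P1 = 0.28, P2 = 0.0097, two-sided 5%, 80% power. P is taken as the mean of the two rates, 0.14485.

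n = (1.960 + 0.842)² × 2 × 0.14485 × 0.85515 / (0.2703)² = 26.6, so 27 per group.

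27 / 0.90 = 30 per group, and 4 × 30 = 120. The stated figures reproduce.

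**3. Power at 27 per group, same formula.**

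Power = Φ( |P1 − P2| × √[27 / (2P(1 − P))] − 1.960 ) = Φ(2.822 − 1.960) = 80.6%.

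**4. Effect of participants who cannot respond.** Let a share f start below 20. This share is assumed, because the article gives no baseline distribution. If 28% and 0.97% are response rates among people able to respond, both are multiplied by (1 − f). The difference then shrinks from 27.0 to 27.0 × (1 − f) percentage points.

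| f (assumed) | Rates | Power at 27 per group | Per group for 80% | Total with 10% dropout |
|---|---|---|---|---|
| 0 | 28.0% v 0.97% | 81% | 27 | 120 |
| 5% | 26.6% v 0.92% | 78% | 29 | 132 |
| 10% | 25.2% v 0.87% | 76% | 31 | 140 |
| 20% | 22.4% v 0.78% | 70% | 35 | 156 |
| 30% | 19.6% v 0.68% | 63% | 40 | 180 |

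**5. Which analysis this touches.** The table applies to a comparison of responder proportions. Statistical analysis plans repeated measures comparisons at weeks 4, 8 and 12 but does not say whether the variable is the THI score or the response. On the score, a participant at 18 can still improve by up to 18 points and so contributes information, though with limited room.

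**The case against.** A reader might infer that low scorers dilute every comparison in the trial. The article does not support that. It names the THI as primary outcome, lists analysis of variance for numerical variables, and ties no stated comparison to the response definition; the chi-square test is listed only for categorical variables in general. If the repeated measures analysis uses the score, these participants face a floor but are not excluded from showing benefit.

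The size is also uncertain, for three reasons.

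- The share below 20 is unknown and could be close to zero.
- The feasibility study behind the 28% and 0.97% is not shown. If it enrolled low scorers, those rates already reflect them in part, so it cannot be said that the planning figures make no allowance.
- Statistical methods calls the figures a mean decrease rate, not a responder proportion. If they are mean percentage falls, scaling them by (1 − f) has no clear meaning. That is a separate problem with the sample size.

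At the low end the loss is modest: with f = 10% and all 30 per group analysed, the same formula gives about 80%.

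Two further inferences should be resisted. Recomputing at a Bonferroni level would show much lower power, but that drop is present at f = 0 and belongs to multiplicity. A chance imbalance in low scorers between arms is part of the sampling error that the test already allows for; it costs precision and does not bias the comparison.

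These objections limit the scope and size of the point. They do not remove the mismatch itself. The article prints its inclusion list as the full set of conditions, so condensation from a longer protocol is a weak explanation.

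**Conclusion.** The point holds in a limited form. Anyone entering with a THI of 18 or less is a non-responder by construction, which follows from the scale, the response definition and the entry lists without any assumption. The consequence is certain for the responder proportion, the scale on which the trial was sized. For an analysis of the score it is only a softer floor effect. The fall from 81% to about 76%, 70% or 63% is illustrative. It rests on assumed shares of 10%, 20% and 30%, and on reading the plan's rates as response rates among people able to respond. The trial remains interpretable; this is an avoidable loss that can be removed cheaply.

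**What to change.** 1. State the baseline-adjusted continuous THI score as the primary variable in the repeated measures analysis, so that low scorers contribute, and make the 20-point response secondary. This costs almost nothing, because the score is already collected at every visit.
2. For participants still to be enrolled, require a baseline THI of at least 20. This is the lowest score from which the trial's own response is possible. Baseline THI is already measured before randomization, and Trial status says that recruitment is under way.
3. Keep everyone already enrolled, including those below 20, and describe participants enrolled before and after the change separately.

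The cost is one eligibility amendment. Some people with slight tinnitus will be turned away, and the trial will have two eligibility rules, which must be reported.

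### Single-step Bonferroni is valid here, but a step-down adjustment over all six contrasts would keep the same 5% error rate and modestly raise power in some scenarios

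*Protocol article*

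**What the plan says.** The Statistical analysis section of the protocol article sets out two steps. The first compares each ear-stimulation arm with the acupuncture control: "ABVN plus tone versus electrical acupuncture, non-ABVN plus tone versus electrical acupuncture, and ABVN versus electrical acupuncture". Three visits are named for these comparisons, in weeks 4, 8 and 12. The second step is conditional: "If a significant difference is found, the next step is to make comparisons among the three treatment groups in effectiveness". Three arms give three pairs, so the two steps together hold six contrasts at a visit, which are all the pairs of four arms. One sentence covers multiplicity: "Multiple comparisons will be adjusted according to the Bonferroni correction method". It gives neither the divisor nor the set of contrasts it applies to, and it does not say whether the three visits count.

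The sample size, under Statistical methods, is 27 evaluable patients per group: "The required sample size is approximately 27 participants for each group".

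**The concern.** Single-step Bonferroni holds every contrast to the same strict threshold, even after earlier rejections have ruled out many of the ways in which the remaining null hypotheses could all be true. A step-down procedure uses that information. It needs no further assumption, keeps the same family-wise error rate over the same set of contrasts, and never rejects less.

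The aim is to learn whether vagal-branch stimulation alone or its combination with sound matters more. That question depends on contrasts among the ear-stimulation arms, and more than one may be needed for an answer. The article itself lists a relatively small sample as a limitation. With the numbers fixed and recruitment under way, the testing rule is one of the few places left to recover some power.

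**Working it through.** **Planning figure.** Inputs from Statistical methods: rates 0.28 and 0.0097 ("the mean decrease rate is 28% in the VNS group and 0.97% in the control group"), two-sided 5%, 80% power. P = (0.28 + 0.0097)/2 = 0.14485. n = (1.960 + 0.842)² × 2 × 0.14485 × 0.85515 / (0.28 − 0.0097)² = 7.849 × 0.2477 / 0.07306 = 26.6, so 27. The figure reproduces, and 27 per arm is used below.

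**Assumptions, not in the article.** One visit, normal outcome, one model with four arms (4 × 26 = 104 df), effects in SD units. The gate is read as at least one rejection against acupuncture at 0.05/3. Critical |t| is 2.433 at 0.05/3, 2.274 at 0.05/2 and 1.983 at 0.05. Power and error come from simulation with at least 200,000 replicates per scenario.

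**Error of the plan as read (gate, 0.05/3 in each step).**
- All four arms equal: a false rejection requires passing the gate, so error is at most 3 × 0.0167 = 5%. Simulated: 4.4%.
- Otherwise at most three of the six nulls can be true, so error is again at most 3 × 0.0167 = 5%.

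The plan therefore controls error over all six contrasts.

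**Gated step-down.** Make the first rejection against acupuncture at 0.05/3. Then test each remaining contrast at 0.05/k, where k is the largest number of remaining nulls that can still all be true. Call the ear arms A, B, C and acupuncture E.
- A–E rejected: B = C = E is still possible, so k = 3.
- A–E, B–E and A–C rejected: at most A = B and C = E remain, so k = 2.
- A–E, B–E and A–B rejected: at most one equality remains, so k = 1.

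Because k never exceeds 3 after the first rejection, this rejects everything gated Bonferroni rejects.

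**Power, gated Bonferroni to gated step-down.**

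| True means A, B, C, E (SD) | Contrast | Bonferroni | Step-down |
|---|---|---|---|
| 0.8, 0, 0, 0 | A–B or A–C | 56% | 56% |
| 0.8, 0.8, 0.8, 0 | all three against E | 47% | 47% |
| 0.8, 0.8, 0, 0 | all four true differences | 37% | 44% |
| 1.4, 0.7, 0.7, 0 | each 0.7 SD contrast | 56% | 60% |

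In the first two rows one arm differs from the other three. Three nulls are then true, k stays at 3 until a true null is wrongly rejected, and almost nothing is gained.

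**Without the gate, Bonferroni to Holm over all six.** In the graded scenario (1.4, 0.7, 0.7, 0) power for the 0.7 SD contrasts goes from 46% to 54%. With 0.8, 0, 0, 0 it goes from 60% to 63% per true difference.

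In both comparisons the chance of at least one rejection is unchanged, since each pair of methods starts from the same threshold.

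**Separate 5% in each step (Holm first, Shaffer second, gate kept).** Suppose A and B are better than C and E. The true nulls are C–E in step one and A–B in step two. Once the false nulls are rejected, each is tested at the full 5%. They share no arm, so error tends to 1 − 0.95² = 9.75%. Simulated error over the six contrasts:
- A and B better by 0.8, 1.0 and 1.5 SD: 8.3%, 9.0% and about 9.7%, against 3.3% for gated Bonferroni.
- A alone better by 0.8 and 1.5 SD: 6.9% and 8.5%, against 4.0% and 4.4%.

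The gated step-down stays at or below about 5% in all of these.

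**The case against.** The strongest objection is that prespecified Bonferroni is valid, that a refinement could be left to an analysis plan not shown here, and that the article contradicts nothing by choosing it. All of that stands. This is a matter of efficiency.

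A reader might infer more: that the plan gives power away for nothing, because Holm in the first step and Shaffer in the second, each at 5%, have the same error rate. Taken one step at a time and ungated, the gains look large. With all three ear arms 0.8 SD from acupuncture, power to detect all three rises from 46% to 64%. With one ear arm 0.8 SD better than the other two, power for both true differences rises from 55% to about 71%. The documents do not support that reading, for three reasons:
- The steps are linked by a gate, and error over the six contrasts rises towards 10%, so part of that gain is bought with false positives.
- The second-step figures ignore the gate. With one ear arm 0.8 SD above the other three arms, power per true difference is 56% to 61%, even at a separate 5% per step.
- The article defines no two families of three. That is an inference, and three visits are also named.

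Bonferroni also has simple simultaneous intervals that match its tests, which step-down methods lack.

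**Conclusion.** The point holds as a modest improvement. Bonferroni is valid, but less efficient than a step-down procedure controlling the same error over the same contrasts. At 27 per arm the gated version gains about nothing when one arm stands apart from the other three, about 4 points per 0.7 SD contrast with graded effects, and about 7 points for detecting all four differences when the arms split two and two. Holm over six gains about 8 points on Bonferroni over six in the graded scenario.

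Holm over six improves on Bonferroni over six, but not necessarily on the gated plan at 0.05/3, since it starts at 0.05/6. In the graded scenario it gives 54% against 56%. The choice between the two versions therefore depends on which reading of the plan is meant.

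The results assume one visit, a normal outcome and the gate as read above. The article gives no effect sizes for the individual contrasts, so the scenarios are illustrative.

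A step-down rule should not be taken to reconcile the adjusted analysis with the unadjusted 5% used for the sample size. That is a separate matter. By the article's own formula, 27 per group gives about 67% power at 0.05/3.

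**What to change.** Replace the Bonferroni sentence with one of the following, and state whether the 5% applies at each visit or across visits:

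- **Gate kept:** *At a visit, the six pairwise contrasts come from one model with all four arms. Contrasts with electrical acupuncture are first tested at 0.05/3. If at least one is rejected, every remaining contrast is tested step-down at 0.05/k, where k is the largest number of remaining null hypotheses that can all be true given the rejections so far (Shaffer). Family-wise error over the six is 5%, two-sided.*
- **Gate dropped:** *Holm's procedure over the six contrasts at a visit, from the same model, two-sided family-wise 5%.*

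If a separate 5% in each step is preferred, say so openly and state that error over the six contrasts can approach 10%.

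The cost is one sentence and a few lines of arithmetic on unadjusted p-values from the planned model, with no extra patients. Step-down p-values have no simple matching simultaneous intervals, so report Bonferroni or ordinary 95% intervals beside them and label which they are. The change should be made before anyone sees outcome data by arm.
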